### Outcomes measures

2.6

Researchers determined that the following data will be collected for observing the characteristics of KM weight loss treatment. Detailed research schedule and variables are presented in Table 2.

(1)*Demographics*: Age, sex, and medical history will be collected as basic demographic information.(2)*Anthropometric data*: If a participant visits physically for consultation, vital signs, including blood pressure, body temperature, and pulse rate will be collected as variables related to general health conditions. Weight, height, and body mass index (BMI) will be measured as variables for weight change. Body fat mass, body muscle, visceral fat level, etc will be measured as variables for changes in body composition.(3)*Liver and kidney function tests*: To evaluate the physical changes induced by long-term administration of HM or weight loss, liver function (aspartate aminotransferase, alanine aminotransferease) and renal function tests (blood urea nitrogen, creatinine) will be conducted at the visit.(4)*Other laboratory test*: Total cholesterol, high-density lipoprotein, low-density lipoprotein, triglycerides, etc will be evaluated at the visit to evaluate the physical changes induced by long-term administration of HM for weight loss.(5)*HM treatment*: For the observation and collection of real clinical data, there will be no restriction on the type or frequency of HM treatment, and doctors in the primary KM clinics will perform the HM treatment according to the characteristics of the individuals. For a given period, prescription medication will be recorded with the name of the medicine, medicine composition, and treatment duration.(6)*AEs*: At each treatment visit, participants will be investigated by the KM doctors using the AEs template developed by the expert Delphi group to evaluate the occurrence of any AE. In case of occurrence of any AE, we will immediately provide appropriate treatment to the participant according to the guidelines of the clinic, and then observe the participant's progress during the follow-up visit. The name, severity, and duration of the AEs that occur during the study period will be recorded. In addition, any causality assessments between the AE and the KM treatment will be evaluated by the investigator during visits. All investigators and KM doctors will be educated in research ethics (Table 2).

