### Sample size calculation

2.8

We plan to recruit at least 1000 patients during this study period. Empirically considering the trends of the patients visiting each primary KM clinics, we estimated that approximately 1000 participants will be enrolled (65 patients or more per year per clinic) for a year. The study started in October 2021, is currently ongoing, and will finish in October 2022.

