### Statistical analysis

2.9

All statistical analyses will be conducted via two-tailed tests, and the significance level will be set at 5%. Categorical variables will be presented as n (%) whereas continuous variables will be expressed as mean ± standard deviation. For comparison of two or more groups, categorical variables will be subjected to the chi-square test and Fisher's exact test, whereas continuous variables will be analyzed using the *t* test and analysis of variance or non-parametric methods, such as Mann–Whitney *U* test and Kruskal–Wallis test, for those not meeting the normality criteria. Pre- and post-treatment comparison conducted with a paired *t* test or Wilcoxon signed rank test will be analyzed using a Kolmogorov–Smirnov test. Analysis of covariance will be performed when it is necessary to control the underlying variables, such as demographic variables. For data with a missing value, the last observation carried forward will be used through case report form (CRF) inspection to replace the missing value. All statistical analyses in this study will be conducted using SAS software, version 9.4 (SAS Institute, Inc., Cary, NC).

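### Enrolment and study close fall in the same month and treatment length is open, so the general rule for continuous variables would understate time on herbal medicine

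*Protocol article*

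**What the plan says.** Two durations are collected under Outcomes measures (2.6). For treatment, "prescription medication will be recorded with the name of the medicine, medicine composition, and treatment duration". For adverse events (AEs), "The name, severity, and duration of the AEs that occur during the study period will be recorded". The same section places no limit on the type or frequency of HM treatment. Table 1 lists an end-of-treatment assessment but gives it no time point.

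The Abstract and Study design/setting (2.1) put recruitment between October 2021 and October 2022. Sample size calculation (2.8) adds: "The study started in October 2021, is currently ongoing, and will finish in October 2022". No follow-up after the last enrolment is stated.

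Statistical analysis (2.9) gives one summary rule, "continuous variables will be expressed as mean ± standard deviation". For comparing groups, "continuous variables will be analyzed using the *t* test and analysis of variance or non-parametric methods", the latter "such as Mann–Whitney *U* test and Kruskal–Wallis test, for those not meeting the normality criteria". For missing data, "the last observation carried forward will be used through case report form (CRF) inspection to replace the missing value". None of these rules excepts durations.

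**The concern.** How long patients stay on HM is a natural part of the registry's first aim, to describe the current status of treatment. For a patient still on HM at closure, the total duration is known only to exceed what has been observed. The rules in 2.9 leave two ways to treat such a patient. One is to enter the time so far as if it were the full course, and carrying the last observation forward does the same. The other is to leave the patient out, which keeps the shorter courses. Both bias the mean downward. The rank tests do not repair this, because they too take a cut-off value as a completed one.

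The registry would then report shorter use of HM than really occurs, and the Discussion says its data are to feed practice guidelines and evidence on HM safety. Observed time also depends on when a patient enrolled, so a clinic that starts late would appear to give shorter courses.

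**Working it through.** **The plan's own figure.** The article gives no treatment length, so there is no duration figure to reproduce. The enrolment figure in 2.8 does reproduce: 15 clinics × 65 patients = 975, against about 1000.

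**Inputs from the article.** Entry over about 12 months, closure in the month in which entry ends, and about 1000 patients.

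**Assumptions.** Entry is uniform, so possible follow-up U is uniform on 0 to 12 months. Treatment duration D has mean m = 1, 3 or 6 months. Two shapes are used: exponential (widely spread) and gamma with shape 4 (less spread).

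**Exponential, closed form.**
- Share still on HM at closure: P(D > U) = (m/12)(1 − e^(−12/m)).
- Mean if cut-off courses are entered as complete: E[min(D, U)] = m × (1 − that share).
- m = 1: share 0.0833 × (1 − e^(−12)) = 8.3%; mean 0.92.
- m = 3: share 0.25 × (1 − e^(−4)) = 24.5%; mean 3 × 0.755 = 2.26.
- m = 6: share 0.5 × (1 − e^(−2)) = 43.2%; mean 6 × 0.568 = 3.41.

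Of 1000 patients, about 83, 245 and 432 would still be on HM at closure.

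**Gamma, shape 4.** E[min(D, U)] is the integral of S(t)(1 − t/12) over 0 to 12 months, where S(t) = P(D > t). It gives 0.95, 2.53 and 4.14 months.

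| True mean (months) | Mean, cut-off courses entered as complete (gamma / exponential) | Too low by | Mean, completed courses only (gamma / exponential) | Too low by |
|---|---|---|---|---|
| 1 | 0.95 / 0.92 | 5% / 8% | 0.98 / 0.91 | 2% / 9% |
| 3 | 2.53 / 2.26 | 16% / 25% | 2.75 / 2.10 | 8% / 30% |
| 6 | 4.14 / 3.41 | 31% / 43% | 4.67 / 2.86 | 22% / 52% |

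If every course had exactly the same length m, the mean of cut-off and complete courses would be m − m²/24, that is 0.96, 2.63 and 4.50 months (4%, 13% and 25% too low).

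**Different entry times, same true mean of 3 months (exponential).**
- Entry in months 0 to 6 (U from 6 to 12): 3 × [1 − 0.5(e^(−2) − e^(−4))] = 2.82 months.
- Entry in months 6 to 12 (U from 0 to 6): 3 × [1 − 0.5(1 − e^(−2))] = 1.70 months.
- False difference: 1.12 months.

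**AE duration.** Assume onset uniform within one month of entry and exponential duration. Onsets before closure then average 11.5 months of entry time, and the shortfall is about m/11.5: 0.25/11.5 = 2%, 0.5/11.5 = 4% and 1/11.5 = 9% for mean durations of about one week, two weeks and one month.

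**The case against.** The strongest reply is that censoring is inferred. The sentence on prescriptions in 2.6 can be read as the length of each prescribed course, which is known when it is prescribed and cannot be censored. Nothing in the article names total time on HM as an outcome to be estimated. That reading is fair, but it does not remove the problem. Anyone who adds up courses to describe how long patients are treated meets the same cut at closure.

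Second, Table 1 has an end-of-treatment visit. If every patient were followed to it, only loss to follow-up would remain. A reader might infer that the rule is wrong wherever the closing date is set. The documents do not support that: the figures above all depend on closure in the month in which enrolment ends.

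Third, a reader might infer that differences between treatments will be shrunk. Section 2.9 provides generic group tests but plans no comparison of durations between treatments. The direction is not fixed either. With the same entry pattern in both groups, a true difference of 1.0 month (2 vs 3) would show as 0.60 (exponential) to 0.74 (gamma), but with different entry times a false difference can appear.

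Fourth, a reader might take AE duration to be equally affected. The bias is only about 2% to 9% for AEs lasting up to a month, so treatment duration carries the point.

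Last, this is a condensed article, duration is a descriptive item, and an analysis plan not shown may treat it separately. That lowers the weight of the point. It does not change the fact that the rule as stated has no exception.

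**Conclusion.** The point holds for total time on HM. With enrolment and closure in the same month, open-ended treatment and the general rule in 2.9, courses still running at closure would be counted as complete or dropped, and the mean would be too low. With cut-off courses entered as complete, the shortfall is 5% to 8%, 16% to 25% and 31% to 43% for true means of 1, 3 and 6 months. If most courses last about a month, the effect is minor; at three months or more it is material. These figures rest on uniform entry, closure at month 12, and assumed mean lengths and shapes. A spurious difference between clinics or groups with different entry times is possible. For AE duration the effect is small when AEs are short.

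**What to change.** In 2.9, exempt total time on HM from the mean ± SD rule and from carrying the last observation forward. Define it as the time from first HM supply to the end of HM, with patients still on HM at closure censored there. Report the Kaplan–Meier median with 95% CI and the proportion still on HM at fixed months. If groups are compared, use the log-rank test or Cox regression.

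Add a sensitivity analysis that counts patients lost to follow-up as having stopped at their last supply. Someone who ceases to attend may well have stopped HM, so censoring at last contact may be informative and push the estimate upward. The Discussion itself notes that follow-up of these patients is difficult.

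Treat AEs unresolved at closure in the same way, or simply report them as ongoing. Confirm that the eCRF distinguishes ongoing from ended treatment and AEs; its fields are not shown, so this cannot be checked here.

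The cost is a few sentences of analysis text and one extra analysis, plus a status field if none exists. The downside is small: the median may not be estimable if many patients are still on HM at closure.

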The purpose of this study is to investigate the clinical characteristics and current status of individuals who receive HM for weight loss in KM by constructing multi-institutional prospective registry. Overall, the aims of this registry are to:

(1)investigate the clinical characteristics and current status of treatment for weight loss;(2)evaluate the safety of various HMs for weight loss, based on nationwide registry outcome collecting process.

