### Study design/setting

2.1

This is a prospective observational multi-center study enrolling patients undergoing KM weight loss treatment in Korea. We will recruit patients from the following 15 KM clinics: Bareun-mom S KM clinic (Hwaseong, Gyeonggi-do), Saeng-saesang KM clinic (Daejeon), Sangju Baraeun KM clinic (Sangju, Gyeongsang-do), Hwapyeong KM clinic (Incheon), Imom KM clinic (Changwon, Gyeongsang-do), Goeun KM clinic (Gunpo, Gyeonggi-do), Lee Seung Jin KM clinic (Namyangju, Gyeonggi-do), Onki KM clinic (Namyangju, Gyeonggi-do), Chunjin KM clinic (Boryeong, Chungcheon-do), Sogood KM clinic (Seongnam, Gyeonggi-do), Gyeongsan S KM clinic (Gyeongsan, Gyeongsang-do), Myoungjak KM clinic (Gunsan, Jeolla-do), Momandjang KM clinic (Gunpo, Gyeonggi-do), Kyurim KM clinic (Cheongju, Chungcheon-do), and Madimadi KM clinic (Yongin, Gyeonggi-do) between October 2021 and October 2022 (Fig. 1). Patients who provide informed consent to participate will receive KM weight loss treatment according to their individual characteristics without any intended intervention. At baseline (recruitment), comprehensive data will be collected on the following variables: demographics, anthropometric information, medical history, laboratory tests, treatment, and AEs. An electronic care report form (eCRF) was developed using the myTrial system^[19]^ of the National Agency for Development of Innovative Technologies in Korean Medicine (IT-KgoM), which supports public eCRFs. Table 1 shows the data collection and follow-up schedules.

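### The named tests assume independent patients, and the plan commits to no clinic effect for pre/post tests or for comparisons whose groups follow clinic

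*Protocol article*

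**What the plan says.** Section 2.9 (Statistical analysis) fixes two-sided testing at the 5% level. On group comparisons it says: "For comparison of two or more groups, categorical variables will be subjected to the chi-square test", with Fisher's exact test alongside. Continuous variables get the t test, analysis of variance, Mann–Whitney or Kruskal–Wallis. Pre/post changes get the paired t test or the Wilcoxon signed rank test. Analysis of covariance is available where adjustment is thought necessary, with demographic variables as the example. No clinic term, clinic stratification, generalised estimating equations (GEE) or cluster-robust variance is named anywhere in the article.

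The sampling structure is clear from other sections. Section 2.1: "We will recruit patients from the following 15 KM clinics". Section 2.8 sets the expected intake at "65 patients or more per year per clinic". On prescribing, section 2.6 item (5) says that "there will be no restriction on the type or frequency of HM treatment" and that "doctors in the primary KM clinics will perform the HM treatment according to the characteristics of the individuals". Under section 2.6 item (6) the Korean medicine (KM) doctors ask about adverse events at each treatment visit. Under section 2.7 the doctor in charge of each clinic enters the data.

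The second aim in the Introduction is to "evaluate the safety of various HMs for weight loss". Section 2.9 does not say which groups will be compared.

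**The concern.** Patients of one clinic share prescribers, adverse-event questioning, data entry and local case mix. Their outcomes are therefore likely to resemble each other more than those of patients from different clinics. A test that counts them as independent then overstates the information in the data.

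Two kinds of planned analysis are exposed. The first is the pre/post test, where the mean change may differ between clinics. The second is any comparison whose groups follow clinic, and herbal medicines are the obvious candidate because the prescriber belongs to the clinic. In the second case there is also possible bias: a formula used mainly in a few clinics would carry those clinics' recording habits and patients into its apparent safety profile.

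The Discussion says the data will be used to verify hypotheses, including the safety of herbal medicine, and will feed clinical practice guidelines. It also refers to 14,106 primary KM clinics. The inference is thus meant to reach beyond the 15 taking part, and variation between clinics belongs in the standard error.

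**Working it through.** **Inputs.** From the article: 15 clinics (2.1), at least 1000 patients (2.8), two-sided 5% (2.9). Assumed, because the documents give no value: ICC of 0.01 to 0.10, and clinics of equal size.

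**The plan's own figure.** 15 × 65 = 975 is a floor, and 1000 / 15 = 66.7 per clinic. Section 2.8 says 65 or more per clinic and approximately 1000 in total, so the figures agree. This is a feasibility estimate, and there is no power calculation to reproduce.

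**Design effect.** With m = 66.7 patients per clinic, for an overall mean change or a comparison with exposure fixed by clinic:

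- DE = 1 + (m − 1) × ICC
- effective N = 1000 / DE
- factor by which the standard error is understated = √DE
- true type I error of a nominal 5% test = 2 × [1 − Φ(1.96 / √DE)]

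Example at ICC 0.05: DE = 1 + 65.7 × 0.05 = 4.28; √4.28 = 2.07; 1.96 / 2.07 = 0.95; 2 × [1 − Φ(0.95)] ≈ 34%.

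| Assumed ICC | DE | Effective N | SE factor | True type I error |
|---|---|---|---|---|
| 0.01 | 1.66 | 604 | 1.29 | 13% |
| 0.02 | 2.31 | 432 | 1.52 | 20% |
| 0.05 | 4.28 | 233 | 2.07 | 34% |
| 0.10 | 7.57 | 132 | 2.75 | 48% |

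**Check by simulation.** Fifteen clinics of 67 patients, a normal outcome with no true effect, t tests that ignore clinic, 4000 runs per setting. Rejection rates at a nominal 5%:

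| Situation | ICC 0.01 | ICC 0.05 | ICC 0.10 |
|---|---|---|---|
| Pre/post test | 12% | 34% | 48% |
| Exposure fixed by clinic | 13% | 35% | 49% |
| Exposure share varies between clinics (uniform 0 to 1) | 7% | 17% | 27% |
| Exposure balanced within every clinic | 4% | 5% | 5% |

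The first two rows agree with the formula. The third shows that exposure need not be fixed by clinic for the level to be lost. The fourth shows that the problem disappears when each clinic contributes equally to both groups. The pre/post row needs no assumption about how herbal medicines are spread over clinics.

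**The case against.** Several objections have weight.

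- **Not every test is affected.** A reader might infer that all the listed tests have standard errors that are too small. That is wrong: comparisons balanced within clinics, possibly sex or age group, keep their level.
- **Confounding is not documented.** A reader might infer that the herbal medicine given is largely determined by clinic. The article does not say so. Treatment is individualised to the patient, the spread of formulas over clinics is not given, and no comparison between herbal medicines is spelled out. Recording is also partly standardised, by one adverse-event template for all clinics and by periodic review and queries from a clinical research associate. Causality is assigned to the investigator, so it cannot be assumed to be another judgement by the prescribing doctor. Confounding is a risk that follows from the structure, and no more than that.
- **No stated sample-size claim fails.** The 1000 is a recruitment estimate without a power claim, so the effective N figures overturn nothing. Nor is 975 against 1000 a contradiction, given the wording of section 2.8. The planned n (%) and mean ± SD summaries do not change.
- **The full protocol or analysis plan may add detail, and the analysis of covariance could include clinic.** Its wording is open-ended, so clinic is not excluded. But it is optional, does not commit to clinic and does not suit a binary adverse-event outcome. A clustered analysis would also have to replace the tests named in section 2.9, not merely elaborate them.

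What remains is that the article assigns independence-based tests to pre/post changes and to undefined group comparisons in clustered data.

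**Conclusion.** The concern holds for pre/post tests and for comparisons whose groups follow clinic. Carried out as written, these are anti-conservative whenever the ICC is above zero and the conclusion is meant to extend beyond the 15 clinics. The size rests on an ICC that the documents do not give. Over 0.01 to 0.10, the true error rate at a nominal 5% runs from about 13% to 48% for pre/post tests or exposure fixed by clinic, and from about 7% to 27% when the exposure share only varies between clinics. The simulation used t tests on a continuous outcome; the chi-square and rank tests rest on the same independence assumption but were not simulated.

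Possible confounding of herbal medicine with clinic is a separate matter of bias, and its extent cannot be judged from the article. The descriptive aim is not undermined. This is a correction to the inferential part of section 2.9.

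**What to change.** Amend section 2.9 as follows.

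- **Pre/post analyses:** use a mixed model with a random clinic intercept, or GEE, with a small-sample correction suited to 15 clusters (for example Kenward–Roger degrees of freedom in the mixed model).
- **Herbal-medicine comparisons:** estimate the contrast within clinic, through a fixed clinic effect, clinic stratification or a clinic-mean-centred exposure. A random intercept alone still mixes within-clinic and between-clinic information. Label contrasts not estimable within clinic as descriptive.
- **Adverse events:** use a logistic version of the same model.
- **Covariates:** adjust for the baseline value where one is collected. Table 1 records no adverse events at baseline, so this cannot apply to them.

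The cost is wording and programming. SAS is already the stated software, enrolment is by clinic so clinic should be identifiable, and no extra patients or visits are needed. The downside is wider intervals, and some herbal medicines may not be comparable at all.

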**Figure 1 F1:**
[figure not shown]
Study flow chart. BMI = body mass index, BP = blood pressure, KM = Korean medicine.

**Table 1 T1:** Study schedule of the registry study.

	Enrollment baseline	Subsequent visits	End of treatment
Informed consent	V		
Eligibility screening	V		
Demographic characteristics	V		
Body mass index	V		V
Body composition test	V		V
Liver function tests	V		V
Kidney function tests	V		V
Herbal medicine	V	V	V
Blood pressure, body temperature, pulse rate	V		V
Adverse event		V	V

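### On the Table 1 schedule, last observation carried forward sets the change to zero for every patient with a baseline but no end-of-treatment value, and can only undercount new laboratory abnormalities

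*Protocol article*

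**What the plan says.** Section 2.9 (Statistical analysis) states a single rule for incomplete data: "For data with a missing value, the last observation carried forward will be used", by way of CRF inspection. It makes no exception for variables measured twice or for safety data. The same section tests pre-to-post change with a paired t test or a Wilcoxon signed rank test.

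Table 1 has three timing columns: "Enrollment baseline Subsequent visits End of treatment". The rows for BMI ("Body mass index V V"), body composition ("Body composition test V V") and liver tests ("Liver function tests V V") are each ticked in the first and last column, with the middle cell empty. The rows for kidney tests and vital signs are ticked the same way. Only herbal medicine and adverse events are ticked at subsequent visits.

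The Introduction names the safety of herbal medicines as the second aim. Section 2.6 says that the liver and kidney tests are there to evaluate physical changes from prolonged herbal treatment or from weight loss. Section 2.4 lets participants withdraw at any time. No expected dropout rate is given.

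**The concern.** Carrying the last observation forward presupposes intermediate measurements. Where a variable has only a baseline and an end value, a patient without the end value has nothing to carry but the baseline. The rule then amounts to baseline carried forward, and the imputed change is zero by construction.

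There are two consequences. For weight, BMI and body composition, the reported mean change mixes real changes with assigned zeros, and its standard error is calculated as if every zero had been measured. For liver and kidney tests, a patient with a normal baseline who leaves before the final blood test is counted as having stayed normal. The six adverse event types that the Discussion lists for the template are symptoms (headache, nausea, palpitations, dry mouth and thirst, constipation, insomnia). The blood tests are therefore the main systematic check on liver and kidney function, and the Discussion intends the safety results to feed into clinical practice guidelines.

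**Working it through.** **Inputs from the document.** The recruitment target is 1000 (section 2.8). It rests on clinic throughput: 15 clinics × 65 per year = 975, which agrees with 1000 because 65 is stated as a minimum. Measurement times are from Table 1; the missing-data rule and the paired tests are from section 2.9.

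**Assumptions, because the document gives no figures.** Missing fraction d from 10% to 50%; completers' mean weight change −5 kg with SD 4 kg; a new laboratory abnormality in 2% or 1% of completers. All 1000 patients are taken to have a baseline value.

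**Step 1: imputed change.** For a patient without an end value, imputed end − baseline = baseline − baseline = 0.

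**Step 2: mean change.** Mean under the rule = (1 − d) × completers' mean.
- d = 10%: 0.9 × (−5) = −4.5 kg
- d = 30%: 0.7 × (−5) = −3.5 kg
- d = 50%: 0.5 × (−5) = −2.5 kg

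**Step 3: standard error.** Variance of the mixed data = (1 − d) × 4² + d(1 − d) × 5².
- d = 30%: 0.7 × 16 + 0.21 × 25 = 16.45; SE = √(16.45/1000) = 0.128. On the 700 measured: 4/√700 = 0.151.
- d = 50%: 0.5 × 16 + 0.25 × 25 = 14.25; SE = √(14.25/1000) = 0.119. On the 500 measured: 4/√500 = 0.179.

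**Step 4: direction of the error in weight.** True mean = (1 − d) × completers' mean + d × dropouts' mean. At d = 30%, where the rule always gives −3.5 kg:
- dropouts changed by −5 kg: true mean −5.0 kg, so the loss is understated
- dropouts changed by −2 kg: −3.5 − 0.6 = −4.1 kg, understated
- dropouts changed by +1 kg: −3.5 + 0.3 = −3.2 kg, overstated

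**Step 5: new laboratory abnormalities.** Cases counted under the rule = 1000 × (1 − d) × completers' rate; dropouts with a normal baseline contribute none.
- 2% in completers, d = 30%: 14 cases. On those tested, 14/700 = 2.0%; under the rule, 14/1000 = 1.4%.
- 1% in completers and in dropouts, d = 30%: 7 counted against 10 true cases, so 30% are missed.
- 1% in completers and 3% in dropouts, d = 30%: 7 counted against 7 + 9 = 16, so 56% are missed. At d = 10% the figures are 9 against 12 (25% missed); at d = 50%, 5 against 20 (75% missed).
- No cases seen: the one-sided 95% upper bound, 1 − 0.05^(1/n), is 0.30% if 1000 are treated as tested and 0.43% on the 700 actually tested.

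**The case against.** Several points on the other side are sound.

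- **Weight.** A reader might infer that weight loss is biased by exactly the missing fraction. That holds only if dropouts would have changed as completers did. Step 4 shows that the error can go either way, and if dropouts returned to their baseline weight the rule would give the right mean.
- **False positives.** A reader might also infer that the smaller standard error inflates the paired test. On these figures it does not: mean/SE is 3.5/0.128 = 27 under the rule against 5.0/0.151 = 33 on observed data. The fault is false precision around a mean that includes invented values.
- **Adverse events.** To say that the rule hides toxicity in general goes too far. Table 1 and section 2.6 have adverse events asked about at each treatment visit, so those reported before dropout stay visible. Nor does the article define a rate of abnormal liver or kidney tests as an endpoint; it speaks of physical changes.
- **Timing.** Section 2.6 says "If a participant visits physically for consultation, vital signs, including blood pressure, body temperature, and pulse rate will be collected", places the laboratory tests at the visit without saying which, and lists lipids that Table 1 omits. Section 2.7 refers to measurements assessed at each visit. Interim values may therefore exist, and the rule would then carry those. End of treatment also has no fixed date, so a patient who stops early but attends a final visit needs no imputation.
- **Design.** This is a descriptive registry. Section 2.5 sets it apart from efficacy trials, and the Discussion acknowledges the limits of the design.

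These points narrow the concern but do not rescue the rule. None of the looser wording sets a schedule different from Table 1. A carried interim value would still be one imputed value treated as data. The reference to CRF inspection is unclear, but does not change which value is carried. A separate analysis plan might add detail, but the fault here is in a rule that the protocol states.

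**Conclusion.** The concern holds in this form: on the Table 1 schedule, the stated rule assigns zero change to each patient with a baseline and no end value, for BMI, body composition, liver tests, kidney tests and vital signs. That mechanism follows from the document alone. The sizes shown are illustrative, because no dropout rate, weight change, SD or abnormality rate is stated.

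For weight, the reported change is shrunk towards zero relative to completers by the factor (1 − d); its error relative to the truth is unknown in direction. For newly abnormal liver or kidney results the error has one direction: carrying a normal baseline forward undercounts, or at best equals, the true number. If dropouts have the same risk as completers, a share d of cases is missed; if their risk is higher, more. This biases the laboratory part of the safety aim towards a reassuring answer. The document does not support extending that conclusion to symptomatic adverse events recorded before dropout. The sentence should be corrected before any analysis.

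**What to change.** In section 2.9, delete the carry-forward sentence and replace it with the following.

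- **Safety laboratory tests and vital signs:** no imputation. Report on patients with a post-baseline value, and state the number tested and the number missing. This corrects the denominator; it does not recover abnormalities in patients who were never retested, which is why the number missing must appear beside the result.
- **Weight, BMI and body composition:** a likelihood-based model on the observed data, or multiple imputation, using variables that the registry collects: baseline value, age, sex, clinic, treatment duration and adverse events. Reason for stopping is not among the listed variables, so the model should not depend on it.
- **Sensitivity:** with two time points these methods lean mainly on baseline covariates and assume data missing at random. Add a missing-not-at-random analysis that varies the dropouts' assumed change. Baseline carried forward may be shown only as a sensitivity analysis labelled as such.
- **Schedule:** reconcile Table 1 with section 2.6 on whether vital signs and laboratory tests, including lipids, are also taken at intermediate visits.

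The cost is one paragraph and a little more programming in SAS 9.4, with no new data collection. Safety denominators will be smaller and confidence intervals wider.
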